**Statistical power:** We plan with 12 sites in 2 phases (intervention and control phase). At least 18 patients per site and phase in 12 sites will be required, thus  $n=432$  in total; accounting for a patient drop-out of maximally 10%, 480 patients need to be included in total. Collecting data over 12 months per phase ensures inclusion of a sufficient number. Estimation of infection risk differences between intervention and control phases will be performed using generalized estimating equations (GEE) models for binary endpoints with identity link; test of non-inferiority with margin of 0.05 using one-sided significance level of 0.05

**Conclusions:** BALTIC should contribute to better evidence on the effectiveness of hand disinfection and extended barrier precautions in critically ill newborns. Further benefits include comprehensive multi-center data collection on MDRO colonization dynamics, an improved awareness on IPC strategies and establishment of network platforms including antimicrobial stewardship programs.

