#### *Sample size calculation and statistical analysis*

GNN and PRIMAL centers treat on average 150 preterm and critically ill neonates per year with compulsory colonization screening. The center-specific rates of Gram-negative HA infection ranges between 1.5 and 6%. Based on single center data as described above and other cohort studies (20-22) we expect 10% of these infants to be colonized with 2MRGN during hospital stay, i.e. 180 infants per 12 months observational period.

Based on previous data, we assume an intracluster correlation of maximally 0.01. Given that the observed correlation is very low, the time lag between the two trial periods is long and different patients are included in the two trial periods at each site. No carry-over effects are assumed, as we are not expecting that effects of one treatment period would influence the second period (after cross-over) since medical care-givers are aware of the study period they are in. Data from two periods at one site are regarded as two independent sites. We further assume a frequency of Gram-negative HA infections in the controls of 3% and a non-inferiority limit of 5%. Striving for a power of 0.8 ( $1-\beta$ ) with a one-sided significance level  $\alpha$  of 0.05, at least  $n=18$  patients per site and phase are required for analysis with 12 sites, thus  $n=432$  in total. To allow for a maximal drop-out of 10% drop-out, at least 480 patients need to be included.

The primary data analysis will be performed according to the intention-to-treat principle (non-linear mixed effect regression models, logit link). Generalized estimating equations are performed to determine the infection rates between the two regimens. Secondary endpoints are analysed as the primary endpoint per individual or per cluster.

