### 9.3 Analysis of Primary Outcome Variables

Based on previous data, we assume a correlation within sites and phases of maximally 0.01. Given that the previously observed correlation is very low, the time lag between the two trial phases is long and different patients are included in the two trial phases at each site, no carry-over effects are assumed. We thus are not expecting that effects of one treatment phase would influence the second period after cross-over, so that data from two phases at one site are regarded as independent.

For the primary analysis, we estimate a GEE model, taking a possible correlation within the phases at one site (cluster as defined above) into account. Assuming a very low intra-cluster correlation, we use the independence structure for the working correlation. To obtain an estimate of the risk difference, an identity link is used. To test for non-inferiority, a margin of 0.05 has been defined.

|                         |                                                                                                                                         |
|-------------------------|-----------------------------------------------------------------------------------------------------------------------------------------|
| Outcome variable        | Anzahl_gramNeg_nurLOS, Anzahl_gramNeg_nurLOS_negativ                                                                                    |
| Endpoint                | Gram-negative BSI                                                                                                                       |
| Effect measure          | Risk difference                                                                                                                         |
| Primary Estimand |                                                                                                                                         |
| Population              | Newborns requiring intensive care in one of the participating NICUs undergoing KRINKO screening and being treated with hygiene measures |
| Treatment               | Standard hygiene measures (hand disinfection plus gloves and gowns, CO) versus hand disinfection only (IV)                              |
| Hypothesis              | Non-inferiority, i.e.
$H_0$ : Risk for gram-negative BSI in IV – Risk for gram-negative BSI in CO group $\geq 0.05$                  |

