|                                                  | $H_1$ : Risk for gram-negative BSI in intervention group – Risk for gram-negative BSI in control group < 0.05                                                                                                                                                                                                                                                                                                                                                                                                                                                                                                                                                                                                                                                                                                                                                                                                                                       |
| Significance level                               | 0.05 (one-sided)                                                                                                                                                                                                                                                                                                                                                                                                                                                                                                                                                                                                                                                                                                                                                                                                                                                                                                                                    |

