| Adjustments for covariates                       | None                                                                                                                                                                                                                                                                                                                                                                                                                                                                                                                                                                                                                                                                                                                                                                                                                                                                                                                                                |
| Main estimator                                   | 
Risk difference is estimated from a GEE logistic regression model with identity link using the following command from the R-library geepack:
 <pre>geeglm(cbind(Anzahl_gramNeg_nurLOS, Anzahl_gramNeg_nurLOS_negativ) ~ Randomisierung, family = binomial(link = "identity"), id = Cluster, corstr = "independence")</pre> 
with the variable <code>Randomisierung</code> indicating the phase (CO vs. IV)
 
From this model, the 95% confidence interval for the risk difference and the one-sided p-value are estimated.
                                                                                                                                                                                                                                                                                                                                                                                                         |

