| Missing data                                     | Analyses are based on complete cases                                                                                                                                                                                                                                                                                                                                                                                                                                                                                                                                                                                                                                                                                                                                                                                                                                                                                                                |
| Interpretation for the primary estimand          | If non-inferiority is statistically significant it is shown that newborns requiring intensive care being treated in a NICU with a hand disinfection only-protocol do not have a higher risk of gram-negative infections than corresponding newborns treated in a NICU with a standard protocol.                                                                                                                                                                                                                                                                                                                                                                                                                                                                                                                                                                                                                                                     |

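### The SAP's pre-specified conclusion says the risk is not higher, but a significant non-inferiority test shows only that any increase is below 5 percentage points

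*Combined protocol and SAP*

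**What the plan says.** The primary analysis table in SAP section 9.3 sets the null hypothesis as a risk difference (hand disinfection only minus standard protocol) of 0.05 or more. The alternative is "Risk for gram-negative BSI in intervention group – Risk for gram-negative BSI in control group < 0.05". The text above the table states "To test for non-inferiority, a margin of 0.05 has been defined". The level is one-sided 0.05, in agreement with the protocol synopsis: "test of non-inferiority with margin of 0.05 using one-sided significance level of 0.05".

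The row of that table on interpreting the primary estimand then says what a significant result shows: newborns in a unit using hand disinfection only "do not have a higher risk of gram-negative infections than corresponding newborns treated in a NICU with a standard protocol". The row does not mention the margin.

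For reporting, the main-estimator row says that "the 95% confidence interval for the risk difference and the one-sided p-value are estimated". It does not say whether the interval is one- or two-sided, and no rule compares a confidence limit with the margin.

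The sample size section of the protocol assumes a 3% control risk, a 5% limit, an intracluster correlation of at most 0.01 and 80% power.

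**The concern.** A non-inferiority test that rejects a difference of 0.05 or more excludes only an increase of that size. It does not address whether there is a smaller increase. The pre-specified reading drops this qualification and asserts no increase at all.

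The gap matters because the margin is large relative to the baseline. Five points on a 3% control risk spans everything from no change to more than a doubling. The endpoint is Gram-negative bloodstream infection in newborns needing intensive care, and the sentence is the SAP's formal conclusion rule for the primary estimand. A report that follows it could state as shown something the trial did not test, and in some datasets something its own confidence interval contradicts.

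**Working it through.** **Inputs.** Control risk 3%, margin 0.05, one-sided alpha 0.05, power 0.80, intracluster correlation 0.01, 18 infants per site and phase, 12 sites, about 150 screened infants per centre and year (protocol, sample size section). The analysis denominator is the number of admissions (SAP section 5).

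**The plan's own size.** I assume a true difference of zero, which the protocol does not state. The Farrington-Manning score formula gives 182.6 infants per arm before clustering, or 182.6/12 = 15.2 per cluster. Allowing for the design effect, m = 15.2 × 0.99/(1 − 0.152) = 17.8, so 18. Then 18 × 24 = 432 in total (216 per regimen), and 432/0.9 = 480. The stated figures reproduce.

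**What the alternative hypothesis contains.** At a control risk of 0.03, every risk under hand disinfection only below 0.03 + 0.05 = 0.08 satisfies it.

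**Illustration at about 1,800 per regimen.** Each site spends 12 months in each regimen, so 12 × 150 = 1,800. This is an assumption about actual admissions, not the plan's stated minimum. The design effect is 1 + (150 − 1) × 0.01 = 2.49. Take observed risks of 5.5% and 3.0%:

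- SE = √[(0.03 × 0.97 + 0.055 × 0.945) × 2.49/1800] = 0.0106
- 95% CI: 0.025 ± 1.96 × 0.0106 = 0.004 to 0.046
- z = (0.025 − 0.05)/0.0106 = −2.36, one-sided p = 0.009

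Non-inferiority is met, the interval lies wholly above zero, and the SAP's sentence would say the risk is not higher. At this size and a 3% control risk, that happens for observed increases of about 2.0 to 3.2 points (about 1.2 to 3.8 points without clustering).

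**The stated minimum, 216 per regimen.** A significant increase needs RD > 1.96 SE. A passed test needs RD < 0.05 − 1.645 SE. Both together need SE < 0.05/3.605 = 0.0139. At a 3% control risk the SE is at least √(2 × 0.03 × 0.97/216) = 0.0164, even with no clustering and no increase. The two results therefore cannot occur together.

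**The sentence can still be untrue at that size.** With design effect 1 + 17 × 0.01 = 1.17, suppose the true risks are 5.5% and 3.0%. Then SE = √(0.0811 × 1.17/216) = 0.0210. The test is passed with probability of roughly Φ(0.025/0.0210 − 1.645) = Φ(−0.45), about one in three. The same approximation at 1,800 per regimen gives Φ(2.36 − 1.645) = Φ(0.72), about three in four. In each such trial the SAP would state that there is no higher risk when the true risk is 2.5 points higher.

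**Interval against test.** A one-sided 0.05 test corresponds to a two-sided 90% interval. At 1,800 per regimen, design effect 2.49, 6% against 3% gives p = 0.033 and a 90% CI of 0.012 to 0.048, with a two-sided 95% CI of 0.009 to 0.051. The two-sided 95% limit can cross the margin when the test is passed.

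All figures use the normal approximation, without a small-sample correction for 24 clusters.

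**The case against.** The best defence is context. The sentence is conditional on a significant non-inferiority test and shares a table with both hypotheses. The protocol's own hypothesis speaks of being not inferior, and the SAP's primary objective is to show non-inferiority. The estimate, the test and the pass/fail decision do not depend on the sentence, and the risk difference is reported with its interval, so an increase would be visible. All of that is true. It does not rescue the wording, because this row exists to say what a significant result shows, and what it says differs from the alternative hypothesis.

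A reader might infer more than the documents support in four ways:

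- **That the direct contradiction arises at the planned size.** The stated size is 432, or 216 per regimen, where it cannot occur at a 3% control risk. The 1,800 rests on average centre volume.
- **That the 95% interval is an error.** The one-sided p-value decides. The interval's sidedness is not stated, and a one-sided 95% bound would match the test exactly. A two-sided 95% interval is only more conservative and leaves the type I error unchanged.
- **That the p-value will be taken against zero** because the model call contains no margin. The SAP asks for a one-sided p-value and states the null at 0.05; it nowhere says that default software output will be used. At most, the formula is not written out.
- **That this sentence will lead units to abandon gloves and gowns.** That is a prediction, and nothing in the documents establishes it.

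**Conclusion.** The concern holds for the interpretation sentence. It claims no increase where the test can show only an increase of less than 5 percentage points. This follows from the SAP's own hypotheses at any sample size. The span up to almost 8% rests on the protocol's 3% control risk. The example of a significantly higher risk reported as not higher rests in addition on about 1,800 admissions per regimen and an intracluster correlation of 0.01.

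The defect is in the conclusion rule. The test, its alpha and the decision are unaffected. The choice of interval and the unwritten test statistic are matters for clarification.

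**What to change.** Replace the interpretation row in SAP section 9.3 with wording such as:

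*If the non-inferiority test is significant, it is shown that the risk of Gram-negative BSI under hand disinfection only exceeds that under the standard protocol by less than 5 percentage points; a smaller increase is not excluded.*

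As an optional clarification, write the test as z = (RD − 0.05)/SE. Report the two-sided 90% CI, whose upper limit is the one-sided 95% bound that matches the test, alongside the 95% CI.

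The cost is a wording change in the SAP with no new data or analysis. The trade-off is that the permitted claim becomes less favourable to the intervention.

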### *Audits*

Quality controls and data security are ensured by the availability of a study protocol, by a monitoring visit prior to the start of the study and by standard operating procedures (SOP, e. g. for diagnosis of sepsis, transmission). Audits are initiated to verify adherence to the study protocol and ICH-GCP (Good clinical practice) procedures.

In order to evaluate the compliance with infection control measures, direct observations are planned on a random basis by the study team and IPC nurses. The observations will not affect

other treatment priorities, e.g. kangaroo care. We aim for anonymous documentation of disinfectant use (nurse, doctor, service staff, parents, others), and compliance with 5 moments of proper hand hygiene, use of gloves and long-sleeved gowns. The Hawthorne effect, i.e. alteration of typical behavior by being observed and variability among observers (external representatives of the study leadership, local hygiene experts, and link nurses) is a potential disadvantage of the direct observation approach (25). We therefore collect data on disinfectant use in the clusters (mL per patient day) which serves as a surrogate for hygiene compliance.

Management of transmissions and possible outbreaks will be at the discretion of the local team based on NICU guidelines which was different across the NICUs. The local standards are documented at initiation of the study-centers, at after 12 months (cross-over) and at the end of the study after 24 months. In the manuscript reporting data we will also report on extended hygiene measures and additional tests for outbreak identification (e.g., genotyping, pulse field electrophoresis)

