### *Outcomes*

The primary endpoint is the rate of HA bloodstream infections with Gram-negative pathogens in all preterm and newborn infants who received colonization screening. This outcome is defined clinically according to NEO-KISS criteria (at least two clinical signs of sepsis + one laboratory sign, e.g. increase in C-reactive protein > 10mg/l) after 72 hours of life and requires the detection of a Gram-negative pathogen in the blood culture. Blood-culture isolates will be sent from the study centers to the study management.

Key secondary endpoint is the 2MRGN transmission rate which is assumed if another infant is colonized with the same 2MRGN pathogen after 2MRGN colonization or infection of an infant

requiring intensive care in a temporal (maximum 90 days) and spatial context (potential contact in the intensive care unit) (26). This assumption is made if, in addition to pathogen identification, the antimicrobial susceptibility testing patterns are identical. Suspected transmission of or bloodstream infection with an 2MRGN pathogen will be reported to the study management as severe adverse event within 24 hours.

Transmission/outbreak management remains the responsibility of the local interdisciplinary infection control team and is carried out according to local standards, including the decision whether to initiate genetic identity testing in the acute situation. 2MRGN isolates will be shipped from local sites and molecular typing will be performed at the Department of Infectious Diseases and Medical Microbiology at the University of Lübeck. Other secondary outcomes at the level of study sites per period ("study phase") are:

- Rate of clinical and culture proven infections
- Rate of infection outbreaks
- Number of initiated antibiotic cycles
- Duration of antibiotic treatment (days)
- Exposure to reserve antibiotics, including Carbapenems per study site in % infants.

To assure documentation of relevant outcomes, intensive interdisciplinary collaboration (neonatology/infectiology/hygiene/pharmacy/management) is required. Data are collected by monthly cluster report forms on infection and transmission rates and yearly surveillance of antibiotic use, disinfectant consumption, and cost estimations.

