| Primary endpoints             | Gram-negative infection in newborn infants requiring intensive care and colonization screening                                                                                                                                                                                                                                                                                                                                                                                                  |
| Secondary endpoints           | 
Patient-level endpoints:
 
 
• any relevant transmission
 
• transmission with 2MRGN
 
• any bloodstream infection (BSI)
 
• 2MRGN BSI
 
• clinical infection
 
 
Month-level endpoints:
 
 
• at least one transmission
 
• at least one transmission with 2MRGN
 
• started antibiotics cycles
 
• percentage of days with antibiotics
 
 |

|                           |                                                                                                                                                                                                                                                |
|---------------------------|------------------------------------------------------------------------------------------------------------------------------------------------------------------------------------------------------------------------------------------------|
|                           | 
 
at least one started reserve antibiotic
 
                                                                                                                                                      |
| Statistical analyses      | Estimation of infection risk differences between IV and CO using generalized estimating equations (GEE) models for binary endpoints with identity link; test of non-inferiority with margin of 0.05 using one-sided significance level of 0.05 |
| Registration of the study | German Trial Register DRKS00019103                                                                                                                                                                                                             |

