| Sensitivity analyses: Confounding         | 
As further sensitivity analyses, the same models are estimated as above with simultaneously taking possible confounders into account:
 <pre>geeglm(cbind(Anzahl_gramNeg_nurLOS, Anzahl_gramNeg_nurLOS_negativ) ~ Randomisierung + Confounder, family = binomial(link = "identity"), id = Cluster, corstr = "independence")</pre> 
with the variable <code>Randomisierung</code> indicating the phase (CO vs. IV) and <code>Confounder</code> being one of the three variables
 
 
• Percentage of shifts with understaffing in the month [<code>GBA_Prozent</code>]
 
• Count of days with blocked beds in the month [<code>Tage_Bettensperrung</code>]
 
• additional workload in the NICU by patients > 28 days of age [<code>Aufnahme_Päd</code>].
 
 
The risk difference with regard to the intervention is estimated accordingly with 95% confidence intervals.
 |
| Hypothesis                                       | n.a.                                                                                                                                                                                                                                                                                                                                                                                                                                                                                                                                                                                                                                                                                                                                                                                                                                                                                                                                                |

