| Significance level                               | Descriptive analysis only                                                                                                                                                                                                                                                                                                                                                                                                                                                                                                                                                                                                                                                                                                                                                                                                                                                                                                                           |
| Supplementary analysis                    | n.a.                                                                                                                                                                                                                                                                                                                                                                                                                                                                                                                                                                                                                                                                                                                                                                                                                                                                                                                                                |

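### The protocol's outbreak outcome has no analysis in the SAP, and one descriptive sensitivity model treats same-month blocked-bed days, a post-randomisation variable, as a confounder

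*Combined protocol and SAP*

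**What the plan says.** **Outbreaks in the protocol.** The Outcomes section lists "Rate of infection outbreaks" among the secondary outcomes per site and study phase. The Synopsis says it is unknown whether extended barrier measures help to prevent outbreaks. The rationale section rests equipoise partly on a possible reduction in outbreaks. Under Audits, "Management of transmissions and possible outbreaks will be at the discretion of the local team", guided by NICU guidelines that differ between units.

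**Outbreaks in the SAP.** The endpoint list in 4.1, the variable tables in section 5, and sections 9.4.1 and 9.4.2 contain no outbreak variable. The nearest endpoints concern transmission, for example "at least one transmission with 2MRGN" at month level.

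**Blocked beds in the SAP.** Section 9.3 adds sensitivity models that refit the primary analysis while "simultaneously taking possible confounders into account". Each adds one of three monthly variables: understaffed shifts (`GBA_Prozent`), "Count of days with blocked beds in the month" (`Tage_Bettensperrung`), or workload from patients older than 28 days (`Aufnahme_Päd`). Their status is "Descriptive analysis only". The only other mention of blocked beds is the plausibility rule in 8.2, which deletes values above 31. No reason for blocking is recorded anywhere.

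**Primary model.** It contains the regimen only. In the 9.3 table, the row "Adjustments for covariates" reads None for the primary estimand.

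**The concern.** There are two separate issues.

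First, a protocol outcome that bears directly on the question of barrier care would go unreported by regimen if the SAP were followed as written. The missing explanation is itself a protocol-SAP mismatch.

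Second, a confounder of the regimen effect has to precede, or at least not result from, the regimen. The order of phases is randomised, and blocked-bed days are counted in the same month as the outcome. If a unit closes beds after infants become colonised or infected, the count is a consequence of the outcome process. Suppose care without barriers led to more outbreaks. Outbreak months would then carry both more Gram-negative bloodstream infections and more blocked beds, and the adjusted model would credit part of the excess to bed closure. The adjusted risk difference would move towards zero. Labelled as control of confounding, it could make the primary result look more robust than it is.

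**Working it through.** **1. Tracing the outbreak outcome through the SAP**

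| Place | Outbreak content |
|---|---|
| Protocol, Outcomes | Listed as a secondary outcome per site and phase |
| SAP 4.1, endpoint list | None; transmission, infection and antibiotic endpoints only |
| SAP 5, source and constructed variables | None |
| SAP 9.4.1, month level | Transmission indicators, antibiotic endpoints |
| SAP 9.4.2, patient level | Transmission, bloodstream infection, clinical infection |

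Transmission endpoints overlap with outbreaks but do not replace them. The month-level versions record at least one event, so a single transmission and a large cluster count the same. At patient level, 9.4.2 lists 2MRGN transmission against the Gram-negative infection variable (`Anzahl_gramNeg_nurLOS_negativ`), so that pairing needs checking before it can serve as a substitute.

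**2. How much of an outbreak-mediated effect the blocked-bed model could remove**

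The plan gives no figure to reproduce here.

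Inputs from the documents:
- 12 sites × 24 months = 288 site-months.
- 150 admissions per site and year, so 150/12 = 12.5 per month.
- Control risk 3% and margin 5 points.

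Inputs assumed, not in the documents:
- An outbreak occurs in 4% of control months and 12% of intervention months.
- There are 2 extra infections per outbreak month, so the risk rises by d = 2/12.5 = 0.16.
- Background blocked days have mean 2 and variance 2.
- A share *c* of outbreaks adds 8 blocked days.

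The whole effect is assumed to run through outbreaks: (0.12 − 0.04) × 0.16 = 0.0128, or 1.28 points.

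For a linear model with equal weight per arm, adjusted difference = total − γ × ΔB, where:
- D = 8*c*, the mean extra blocked days in an outbreak month.
- ΔB = 0.08 × D, the difference between arms in mean blocked days.
- γ = the sum over arms of d·q(1−q)·D, divided by the sum over arms of [2 + q·64*c*(1−*c*) + q(1−q)·D²], where q is the outbreak probability in the arm.

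For *c* = 0.5, D = 4:
- Numerator: 0.16 × 4 × (0.04 × 0.96 + 0.12 × 0.88) = 0.64 × 0.144 = 0.0922.
- Denominator: control 2 + 0.04 × 16 + 0.0384 × 16 = 3.254; intervention 2 + 0.12 × 16 + 0.1056 × 16 = 5.610; sum 8.864.
- γ = 0.0922/8.864 = 0.0104 and ΔB = 0.32.
- Removed: 0.0104 × 0.32 = 0.0033. Adjusted: 0.0128 − 0.0033 = 0.0095. Share removed: 0.0033/0.0128 = 26%.

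The same formula for other values of *c*:

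| Share of outbreaks that close beds | γ | ΔB | Adjusted difference | Share removed |
|---|---|---|---|---|
| 0 | 0 | 0 | 0.0128 | 0% |
| 0.3 | 0.0079 | 0.192 | 0.0113 | 12% |
| 0.5 | 0.0104 | 0.320 | 0.0095 | 26% |
| 0.9 | 0.0134 | 0.576 | 0.0051 | 60% |

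Simulating the 288 site-months under these inputs gave a loss of 24% to 26% at *c* = 0.5 and 55% to 60% at *c* = 0.9. A second assumed set gave about 15%, 40% and 67% at *c* = 0.3, 0.6 and 0.9, and no loss at *c* = 0. That set used outbreaks in 5% of control months against 15% or 25% of intervention months, 15 extra points of risk in outbreak months, and background blocking in 10% of months.

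If outbreaks are equally frequent in both arms, ΔB = 0 and nothing is removed. The unadjusted estimate keeps the full effect in every case. These are linear, admission-weighted fits. The binomial weights of the SAP's model would shift the shares, so they show order of size only.

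**The case against.** A reader might infer that harm acting through outbreaks disappears from the planned results. The documents do not support that. The confirmatory model is unadjusted, so every Gram-negative bloodstream infection arising in an outbreak counts in full. The blocked-bed model is descriptive and only one of several sensitivity analyses. Transmissions, any bloodstream infection, 2MRGN bloodstream infection and clinical infection are all compared by regimen, so a rise in outbreaks would be expected to show there too. Nor does any section say that the adjusted models will be offered as support for non-inferiority.

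The causal link is also an inference. Blocked beds stand in the SAP beside understaffing and extra workload, which suggests a capacity measure. The protocol's own examples of outbreak response are extended barrier precautions and additional typing, not bed closure. Having a separate staffing variable does not settle the matter, because beds may be closed precisely to avoid understaffed shifts.

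The inputs in the illustration are generous. They imply 0.12 × 16 = 1.92 points of outbreak infection in the intervention phase and 0.04 × 16 = 0.64 in control. The protocol cites MRGN infection rates below 0.5%, and the regimens differ only for 2MRGN-colonised infants. Even so, both the unadjusted and adjusted differences lie well inside the 5-point margin.

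Finally, the SAP covers only the biometry institute's analyses, and the protocol promises to report extended hygiene measures and outbreak tests.

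All of this limits the consequence. Two things remain. No section assigns the outbreak rate to anyone else or promises it by regimen. And a variable counted during the randomised phase should not be called a confounder when its causes are unknown.

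**Conclusion.** The point holds in two limited parts.

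The firmer part rests on the text alone: a protocol secondary outcome tied to the trial's question has no variable and no analysis in the SAP, and no explanation is given.

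The second part is conditional. If beds are closed in response to colonisation or infection, the blocked-bed model understates harm acting through outbreaks, by 0% to roughly 60% under the worked inputs and up to about two thirds under the second set. If closures have other causes, nothing is lost. Which case applies cannot be told from the documents.

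The primary non-inferiority test and the sample size are unaffected. The change is worth making because the outbreak question is central to the trial, the correction is cheap, and the model's present label invites a reading it cannot bear.

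**What to change.** 1. Add the outbreak outcome by phase to SAP 9.4.1, for example months with at least one outbreak, using the same descriptive month-level GEE. State the outbreak definition and derive it from the monthly cluster report forms and transmission reports. If this cannot be done, say so and give the reason.
2. Report blocked-bed days by phase as a result in their own right.
3. Drop the blocked-bed model from the confounding analyses. Alternatively, keep it, labelled as adjustment for a post-randomisation variable, with a sentence that it is not to be read as control of confounding or as support for non-inferiority.

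Sites should not be asked for reasons for closure: the documents do not show that these are collected, and obtaining them would mean new retrospective data.

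**Cost:** one more descriptive model, one sensitivity analysis dropped or relabelled, and some work to derive outbreak months, which will be less precise than a variable recorded for the purpose.
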